## Methods

### Design and Setting

The study is designed as a prospective, single-blinded RCT. It will take place in the clinics of Beijing Tongren Hospital, Capital Medical University, and the Acupuncture and Moxibustion Hospital, China Academy of Chinese Medical Sciences (CACMS). Eligible participants will be randomized in a 1:1 ratio to either the EA group (EA plus medication) or the control group (standard medication alone). This pilot trial will apply a longitudinal follow-up design, with a baseline assessment before enrollment (t–1), allocation and intervention initiation at t0, on-treatment follow-ups at week 2 (t1), week 4 (t2), and posttreatment follow-ups at 1 month (t3), 2 months (t4), and 3 months (t5) after intervention completion, barring loss to follow-up. This trial will be reported in accordance with the CONSORT (Consolidated Standards of Reporting Trials)-EHEALTH (see Multimedia Appendix 1) statement, which defines standard reporting items for RCTs [27]. Participant recruitment began on July 15, 2024, with the study scheduled to continue until December 2025. The flowchart is illustrated in Figure 1, and the overall procedure is presented in Table 1.

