**Assessments**																			
	**Feasibility outcomes**																		
		Recruitment rate		N/A		N/A		N/A		N/A		✓		N/A		N/A			
		Adherence rate		N/A		N/A		N/A		N/A		✓		N/A		N/A			
		Data completeness		N/A		N/A		N/A		N/A		✓		N/A		N/A			
		Adverse events		N/A		N/A		✓		✓		✓		✓		✓			

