### Interventions

The control group intervention protocol was designed in accordance with the 2015 Chinese Guidelines for the Diagnosis and Treatment of Sudden Deafness [15]. These guidelines were developed based on extensive RCT data from multicenter clinical studies on sudden deafness in China, incorporating updates from the latest American and German clinical guidelines as well as recent research advancements, ensuring alignment with clinical practice in China [1,4,16]. The treatment regimen for the control group was designed to comprehensively address the inflammation and microcirculatory disturbances associated with ISSNHL through a combination of prednisone, Ginkgo biloba extract, and batroxobin injection. The specific pharmacological interventions are detailed in Table 2.

**Table 2 table2:** Standard treatment regimen for the control group.

Period	Drug	Dosage and administration	Duration
Weeks 1-2 after onset	Prednisone (glucocorticoid)	1 mg/kg/day (maximum 60 mg), oral, once daily in the morning	5 days
Weeks 1-2 after onset	Ginkgo biloba extract	87.5 mg in 250 mL 5% glucose, intravenous infusion, once daily	2 weeks
Weeks 1-2 after onset	Batroxobin injection	5 batroxobin units in 250 mL 5% glucose, intravenous infusion, every other day^a^	2 weeks
Weeks 3-4 after onset	Ginkgo biloba tablets	9.6 mg × 2 tablets, oral, 3 times daily	2 weeks

^a^Before the administration of batroxobin, blood tests are required to confirm fibrinogen levels (>1.5 g/L) and normal coagulation parameters (eg, prothrombin time or activated partial thromboplastin time). Fibrinogen and coagulation function are monitored 24 hours after the first dose and periodically thereafter.

Patients in the EA group will receive the same treatment as the control group, in addition to EA, which will not interfere with their medication treatment.

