The EA group received acupuncture using disposable sterile needles (Hwato Needles; Suzhou Medical Appliance Factory) at acupoints previously identified in studies as functionally related to ISSNHL and tinnitus, including Tinggong (SI19), Tinghui (GB2), Yifeng (SJ17), Yunting area, Anmian, Waiguan (SJ5), Zhongzhu (SJ3), Taichong (LR3), and Taixi (KI3). For limb acupoints, 30-gauge needles (0.25 mm in diameter, 40 mm long) will be inserted to a depth of 10-15 mm. For head acupoints, 32-gauge needles (0.25 mm in diameter, 25 mm long) will be inserted to a depth of 3 mm. A specialized acupuncture technique will be used when needling the Tinggong point (SI19) on the impacted side. The patient will be instructed to slightly open their mouth, and a needle (0.25 mm in diameter, 40 mm long) will be inserted to a depth of approximately 15-25 mm. The assistant will pinch the patient’s nostrils, prompting the patient to take a deep breath, close their mouth, and hold their breath to push air through the Eustachian tube into both ears. During this procedure, the acupuncturist will gently twist the needle until the patient feels a local sensation of soreness or distension. Afterward, the patient will exhale through the mouth, and the acupuncturist will withdraw the needle by approximately 10 mm and leave it in place. Additionally, the Tinghui (GB2) and Yifeng (SJ17) points on the impacted side will be needled and connected to an EA device (KWD-808I type; Great Wall, Yingdi). A sparse wave with a frequency of 2-15 Hz will be applied at an intensity that induces muscle contraction and is tolerable for the patient. The needles will be retained for 30 minutes. Figure 2 provides an operational illustration of the acupuncture technique at the Tinggong (SI19) point, while Figure 3 shows the acupuncture point selection diagram. EA treatment will last for a total of 4 weeks, with 4 sessions per week during the first 2 weeks and 3 sessions per week during the last 2 weeks, conducted every other day.

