### Outcome Measures

#### Feasibility Primary Outcomes

The feasibility primary outcomes are recruitment rate, defined as the proportion of enrolled participants relative to the target sample size; adherence rate, measured as the proportion of participants completing at least 80% of the prescribed EA sessions over 4 weeks, as extracted from treatment logs; data completeness, assessed as the proportion of participants with fully collected baseline and follow-up data for key measures such as PTA and Tinnitus Handicap Inventory (THI); and safety outcomes, recorded as the incidence of adverse events during the treatment period, based on session-by-session reports [31,32].

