As a pilot study, the primary feasibility outcomes include the proportion of enrolled participants relative to the target sample size (recruitment rate, reported as a percentage), the proportion of participants completing at least 80% of prescribed EA sessions over 4 weeks (adherence rate, extracted from treatment logs and reported as a percentage), the proportion of participants with complete baseline and follow-up data for key measures such as PTA and THI (data completeness, reported as a percentage, with the proportion of missing data reported as a complementary indicator), and the incidence of adverse events during the treatment period (safety outcomes, recorded from session-by-session reports and summarized as total events and incidence rate per 100 person-sessions). These feasibility outcomes will be presented using descriptive statistics, without hypothesis testing.

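### The primary safety rate is defined per EA session, so it is undefined for the control arm, and the stated outcome gives no denominator or event source common to both arms

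*Protocol article*

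**What the plan says.** Under Feasibility Primary Outcomes, the protocol article defines safety as "recorded as the incidence of adverse events during the treatment period, based on session-by-session reports". Statistical Analysis repeats this source and adds the summary: events are "recorded from session-by-session reports and summarized as total events and incidence rate per 100 person-sessions". The same paragraph closes with "These feasibility outcomes will be presented using descriptive statistics, without hypothesis testing".

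The Interventions section gives EA over 4 weeks, "with 4 sessions per week during the first 2 weeks and 3 sessions per week during the last 2 weeks". It also states: "Patients in the EA group will receive the same treatment as the control group, in addition to EA". Design and Setting describes the control arm as receiving standard medication only. The adherence outcome also uses the word session for EA: it is "the proportion of participants completing at least 80% of the prescribed EA sessions over 4 weeks".

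Table 1 has a row "Adverse events" under the feasibility outcomes. It is ticked at all five follow-ups, t1 to t5, and is not split by arm. Oversight and Monitoring provides for adverse event records, entry on the case report form and weekly follow-up calls, none of them restricted to the EA arm.

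**The concern.** EA is added to a drug regimen that both arms share, so the useful safety description is what EA adds to the background of drug reactions. That requires a measure that can be formed in each arm, from events looked for in the same way.

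The stated outcome meets neither condition. Its rate has a denominator that exists only in the EA arm. Its named source is a report completed at EA sessions, so the EA arm is observed more often. An EA-arm rate per session then mixes drug reactions with needling events, with no matching control figure to show how much is background.

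The time window is also loosely fixed. The two text definitions stop at the end of treatment, while Table 1 lists adverse events as a feasibility outcome up to 3 months after it. Because the pilot is meant to inform a larger trial, an ambiguous safety measure would be carried forward.

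**Working it through.** The documents state no safety rate, so there is no figure of the plan's own to reproduce. The check is whether the stated rate can be formed in each arm.

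**Inputs**
- EA schedule (Interventions): 4 per week for 2 weeks, then 3 per week for 2 weeks.
- Planned size (Sample Size): 30 per group recruited, 25 per group after allowing for dropout.
- Treatment period: 4 weeks in both arms.
- Control arm: no EA, and no control-arm session is defined anywhere.

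**Denominator by arm**
- Sessions per EA participant: 4 x 2 + 3 x 2 = 14.
- EA arm, full attendance: 30 x 14 = 420 person-sessions.
- EA arm, everyone at the adherence threshold: 0.8 x 14 = 11.2, so at least 12 sessions; 30 x 12 = 360.
- EA arm, 25 participants at full attendance: 25 x 14 = 350.
- Control arm: 30 x 0 = 0, so the rate is undefined.

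**What the choice of denominator does** (event counts assumed for illustration; the documents give none). Suppose 6 participants in each arm have one drug reaction.

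| Measure | EA | Control |
|---|---|---|
| Participants with an event | 6/30 = 20% | 6/30 = 20% |
| Per 100 person-weeks (30 x 4 = 120) | 100 x 6/120 = 5.0 | 5.0 |
| Per 100 person-sessions | 100 x 6/420 = 1.43 | undefined |

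With 3 or 9 events instead of 6, the EA figure per 100 person-sessions is 0.71 or 2.14; control stays undefined. If both arms' events were divided by the EA sessions, the result would be 100 x 12/420 = 2.86, which describes neither arm.

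**Total events alone.** An event total is comparable between arms only if the numbers observed are similar. The Results section reports 21 control and 14 EA completers to date. These are interim counts, not final arm sizes, but they show why a denominator is needed: an assumed 4 participants with an event is 4/21 = 19% in one arm and 4/14 = 29% in the other.

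**Ascertainment.** Under the named source, an EA participant has up to 14 reporting occasions and a control participant none. The weekly calls and scheduled visits apply to both arms, but neither definition of the outcome names them as its source.

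**Window.** The text covers the treatment period, which contains t1 and t2. Table 1 ticks t1 to t5, so three of the five scheduled assessments (t3, t4, t5) lie outside the written definition.

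**The case against.** The strongest reply is that this is a descriptive pilot with no planned test of adverse events between arms, and that a per-session rate is a sensible measure of how well a new procedure is tolerated. Adherence is likewise an EA-only feasibility outcome. Event totals are reported beside the rate, adverse events are recorded for participants generally, and by-arm tabulation is often left to an analysis plan, which is not shown here.

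Much of this stands, and it rules out several stronger readings that a reader might infer:

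- *That adverse events cannot be compared between arms.* The documents do not support this. Total events are a stated summary, allocation is 1:1, the treatment period is common, and events per participant can be tabulated.
- *That control-arm drug reactions have no form to be recorded on.* Oversight and Monitoring covers adverse event records, case report form entry and weekly calls without limiting them to EA. The case report form itself is an appendix not shown, so nothing can be said about what it lacks.
- *That repeat events in one patient are treated as independent.* A descriptive count or rate makes no such assumption, and no standard error, interval or test is specified.
- *That the windows flatly contradict each other.* Events may be collected to t5 and summarized for the treatment period only. What is missing is a statement that this is intended.

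The reply does not remove the core. A descriptive rate still needs a denominator in both arms, and the article does not label this one as EA-only. Nor is this a detail left to another document: the article itself fixes the source and the rate, in two places. Control patients do attend for infusions in weeks 1-2, but the article never calls these sessions. EA patients receive the same infusions, so counting them would change both arms' denominators.

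**Conclusion.** The point holds in a limited form. As written, the primary safety rate exists only in the EA arm (420 person-sessions at full attendance, 360 if everyone attends 12 sessions, against 0 in control). Its named source gives EA patients up to 14 extra chances for an event to be noted. A descriptive comparison can still be assembled from total events and the general records, but the stated outcome neither draws on those records nor supplies a common denominator.

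This rests on reading session as EA session, which is the only use in the article, and on the planned 30 per group. The illustrative event counts are assumptions and do not affect the conclusion. The defect should be corrected before analysis; it is an imprecise outcome definition, not a loss of the trial's safety data.

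**What to change.** 1. Define the safety outcome as the number and percentage of randomized participants with at least one adverse event, plus total events, by arm.
2. Name the source as the weekly calls and scheduled visits already planned, applied identically in both arms.
3. Keep the rate per 100 person-sessions, labelled as an EA-only summary of needling-related events taken from session reports.
4. State in Feasibility Primary Outcomes, Statistical Analysis and Table 1 whether the outcome covers the treatment period only or t1 to t5. If collection runs longer than the outcome window, say so.

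The cost is rewording two sections and Table 1, and slightly more tabulation. EA session reports would no longer serve as the source for the between-arm summary, so an event noted only at a session would appear in the EA-only summary alone. No new data collection is needed, provided the planned calls and visits are recorded for both arms.

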## Results

This study began recruitment on July 15, 2024, and is scheduled to conclude on August 31, 2025. To date, 42 participants have been enrolled, with 35 having completed the intervention and posttreatment assessments (control group: n=21; EA group: n=14). Following protocol publication, data compilation and analysis will be conducted, with results anticipated to be published in a relevant journal in 2026.

## Discussion

### Overview

The treatment guidelines for ISSNHL have been clearly established. However, the treatment protocol for tinnitus, a common comorbid symptom of ISSNHL, remains uncertain [1,47]. This study aims to investigate the potential efficacy and feasibility of EA combined with medication for patients with ISSNHL accompanied by tinnitus. Currently, only a limited number of studies have focused on the treatment of tinnitus, with therapeutic approaches including sound therapy and psychological therapy [48]. Because of the varied nature of tinnitus symptom maintenance, a single treatment modality may not be suitable for all patients [49]. Acupuncture, as one of the most widely accepted complementary and alternative therapies in China, has been explored in prior research for its potential in managing ISSNHL and tinnitus. For instance, Zhou and Jin [50] conducted a retrospective study comparing EA with traditional acupuncture and found that EA was more effective in reducing hearing thresholds and alleviating tinnitus over a 3-month treatment period. Similarly, Zhang et al [51] performed a systematic review and meta-analysis of 12 RCTs, demonstrating that manual acupuncture or EA combined with medication outperformed medication alone in improving hearing outcomes, with some evidence suggesting that EA alone was superior to medication. Additionally, Chen and Jing [52] reported 2 refractory cases where EA alone (12 sessions over 4 weeks) led to complete recovery of unilateral sensorineural hearing loss. However, these findings are limited by low evidence quality and the rare use of tinnitus-specific outcomes (eg, tinnitus matching or THI) as primary end points.

The selection of acupuncture points is primarily based on the following rationale. A study by Huang et al [53] revealed that, through data mining analysis of 112 studies containing 221 prescriptions, the 4 most frequently used acupuncture points were SI19, GB2, SJ17, and SJ3. The SI19-GB2-SJ17 point combination was identified as the core acupoint cluster according to association rule analysis. These peri-auricular acupoints may alleviate tinnitus by stimulating auditory-related nerves and improving blood circulation in the ear region [24,54]. Additionally, scalp acupuncture may exert its effects through the trigeminal nerve and blood circulation regulation, contributing to the improvement of auditory processing and neural activity [55,56].

Most studies currently agree that the earlier patients with ISSNHL receive treatment, the better their prognosis. The study by Byl [57] indicated that patients who received medical attention within 7 days of onset had an approximately 56% recovery rate, whereas those who presented after 30 days had a recovery rate of only 27% (also see [58]). The study by Diao et al [59] also demonstrated that the number of days from onset to treatment was an independent prognostic factor, with shorter time intervals correlating with better outcomes. Therefore, all patients selected for this study were within 7 days of onset. The medication treatment protocol for ISSNHL with tinnitus is the same as that for ISSNHL. The inclusion of multiple variables (ie, multiple drugs) in the standard treatment is driven by the complex pathophysiology of ISSNHL. Research indicates that inflammation is likely a key contributing factor, and corticosteroids such as prednisone are used to reduce inner ear inflammation and edema, thereby improving hearing outcomes [60]. Ginkgo biloba extract, known for its circulation-enhancing and antioxidant properties, may help restore cochlear microcirculation [61]. Batroxobin, a snake venom–derived enzyme with fibrinolytic activity, may improve inner ear blood flow by reducing blood viscosity [62]. This combination of drugs is designed to simultaneously target distinct pathological mechanisms, thereby enhancing overall therapeutic efficacy. The rationale for this combined approach is supported by evidence from studies conducted in China. A retrospective study involving 342 patients with total deafness-type ISSNHL found that adding batroxobin to a treatment regimen of Ginaton and glucocorticoids significantly improved hearing recovery outcomes and maintained plasma fibrinogen levels within a safe and prognostically favorable range [63]. This improvement was particularly notable in terms of hemorheological parameters and peripheral blood T-cell subset reactivity. Additionally, a 2023 meta-analysis further corroborated the efficacy of Ginkgo biloba extract as an adjuvant therapy, suggesting it may outperform corticosteroid monotherapy [64]. These findings support the decision to incorporate multiple pharmacological agents into the standard treatment protocol, aligning with the goal of addressing the multifaceted nature of ISSNHL.

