### Eligibility Criteria

Inclusion criteria included the following: a diagnosis of ISSNHL [15], defined as sudden hearing loss (≥30 dB) within 72 hours affecting 3 consecutive frequencies, and accompanied by tinnitus; between 18 and 65 years of age at the time of recruitment; pure tone audiometry (PTA) results showing a flat drop audiogram; onset of hearing loss within 1 week before randomization; clear consciousness, normal cognition, and unaffected basic communication.

Exclusion criteria were hearing loss from other causes (eg, congenital deafness, conductive deafness, presbycusis, large vestibular aqueduct syndrome, Meniere disease, tumors, or deafness due to systemic genetic diseases); having received medication or acupuncture treatment within the past 6 months, or having an allergy to the treatment medication; pregnancy or lactation in females; presence of severe systemic diseases or psychiatric disorders; and participation in other trials.

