### Enrollment, Randomization, and Blinding

Recruitment will be conducted through WeChat (Tencent Holdings Limited) public account notifications, roll-up banners at clinic entrances, and collaboration with community committees for promotion.

Stratified block randomization will be performed according to the study center. Both groups will be assigned in a 1:1 ratio to the EA and control groups using a block size of 4. [name], a statistician from the Evidence-Based Medicine Center at CACMS, will serve as the randomization coordinator and will be responsible for generating the stratified block randomization sequence using SAS 9.3 software (SAS Institute). She will not participate in the trial’s implementation or data analysis. After obtaining informed consent and before initiating treatment, the treating physician at each center will contact the randomization coordinator by phone to receive the randomization number and group assignment.

Because of the nature of acupuncture, it is not possible to blind the acupuncturists or participants. However, steps will be taken to minimize bias from single blinding as much as possible. Acupuncturists will receive specialized training before participating in the study and will be instructed not to discuss treatment procedures or outcomes. They will also be excluded from evaluating the results. Patients will be treated separately to prevent contact between participants. The randomization staff and acupuncturists will have access to the assignment information, but the outcome evaluators and statisticians will remain blinded throughout the entire clinical trial. Statisticians will speculate on the group allocation before data analysis to assess the efficacy of blinding, and unblinding will only occur after the completion of data analysis.

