### Statistical Analysis

All efficacy analyses will follow the intention-to-treat principle, including all randomized participants. Statistical analyses will be performed using SPSS version 22.0 (IBM Corp). Continuous variables, including PTA, THI, SAS, and SF-36, will be reported as means (SDs) for normally distributed data, or as medians (IQRs) for nonnormally distributed data. Tinnitus matching (frequency and loudness) will be treated as a categorical variable and summarized as proportions or percentages.

Baseline PTA distributions for both groups will be reported as means (SD) or medians (IQRs). Differences in baseline hearing loss severity will be assessed using the 2-tailed (unpaired) independent samples *t* test (for normally distributed data) or the Mann-Whitney *U* test (for nonnormally distributed data). If significant differences are identified, group comparisons will be adjusted for hearing loss severity using analysis of covariance to ensure comparability.

Changes in PTA, THI, SAS, and SF-36 across 6 time points (t0, t1, t2, t3, t4, and t5) will be evaluated using repeated measures analysis of variance for normally distributed data, or the Friedman test for nonnormally distributed data. Changes in tinnitus matching across the 6 time points will be assessed using the Cochran *Q* test to detect overall differences. If significant, pairwise comparisons will be conducted using the McNemar test with a Bonferroni correction for multiple comparisons.

Group differences in PTA, THI, SAS, and SF-36 at each time point will be analyzed using the independent samples *t* test (for normally distributed data) or the Mann-Whitney *U* test (for nonnormally distributed data). If baseline hearing loss severity differs significantly, analysis of covariance will be applied to adjust for this covariate. Differences in tinnitus matching at each time point will be evaluated using the chi-square test or Fisher exact test, as appropriate. Statistical significance will be set at α=.05 (2-sided).

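### Days from onset to treatment is cited as independently prognostic but enters no arm comparison; the cost is some precision and exposure to chance imbalance, of unknown and possibly nil size.

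*Protocol article*

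**What the plan says.** In the Discussion (Overview), the article reports from a cited study that "the number of days from onset to treatment was an independent prognostic factor, with shorter time intervals correlating with better outcomes". It draws one design consequence: "Therefore, all patients selected for this study were within 7 days of onset". Eligibility Criteria sets the matching condition, "onset of hearing loss within 1 week before randomization".

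The allocation scheme balances on one factor: "Stratified block randomization will be performed according to the study center", in blocks of 4.

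Statistical Analysis compares the arms on PTA and THI at each time point with an independent-samples *t* test, or a Mann-Whitney *U* test if the data are nonnormal. It names one covariate and makes its use conditional: "If baseline hearing loss severity differs significantly, analysis of covariance will be applied to adjust for this covariate". The same rule appears earlier in that section, after the baseline test of PTA: "If significant differences are identified, group comparisons will be adjusted for hearing loss severity using analysis of covariance to ensure comparability". Days from onset to treatment is in no stratum, baseline comparison or model that the article describes.

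**The concern.** An entry limit narrows the range of a prognostic factor but does not remove what is left. Participants can still differ by up to a week in time since onset. Design and Setting starts the intervention at t0 and counts visits from there. If treatment starts at randomization, the week-2 visit falls anywhere from 14 to 21 days after onset (14 + 0 to 14 + 7).

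If outcome depends on that interval, part of the spread in PTA and THI is explainable variation that the planned tests leave in the error term. Any chance difference between arms in onset time then goes straight into the estimated effect. This matters modestly here because Sample Size says the pilot will supply effect sizes for planning later trials, and with 25 to 30 per arm chance imbalances are not rare.

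This is more than detail left to an analysis plan. The article states its adjustment rule (which variable, when and by what method), and that rule passes over a factor the article itself cites as prognostic.

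**Working it through.** **Inputs from the article.** Sample Size gives 25 evaluable per arm and 30 recruited per arm. Its total reproduces as 50 × 1.20 = 60. The point does not rest on that figure, which only sets the sizes used below. Eligibility Criteria gives the 0 to 7 day window.

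**Inputs assumed.** The article gives neither the distribution of days within the window nor their correlation *r* with outcome. I take days as uniform on the integers 1 to 7 (SD 2.0) or 0 to 7 (SD 2.29), and *r* = 0.1, 0.2 or 0.3.

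**Step 1: chance imbalance in mean days.** SE = SD × √(2/*n*).
- 30 per arm: 2.0 × √(2/30) = 0.52 day; with SD 2.29, 0.59 day.
- 25 per arm: 2.0 × √(2/25) = 0.57 day; with SD 2.29, 0.65 day.
- Probability that the arm means differ by at least 1 day: 5% to 9% at 30 per arm, 8% to 12% at 25 per arm.

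**Step 2: effect on the arm difference.** A 1-day imbalance shifts it by *r*/2.0 outcome SDs. The unadjusted SE of the difference is √(2/30) = 0.258 SD at 30 per arm.

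| *r* | shift from 1 day | share of SE (0.258) |
|---|---|---|
| 0.1 | 0.05 SD | 19% |
| 0.2 | 0.10 SD | 39% |
| 0.3 | 0.15 SD | 58% |

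A full day is an unfavorable draw. The mean absolute imbalance at 30 per arm is about 0.80 × 0.52 = 0.42 day, which shifts the difference by 0.02, 0.04 or 0.06 SD (8%, 16% or 24% of the SE).

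**Step 3: conditional error rate.** Over all randomizations the unadjusted test keeps its 5% level. Given an imbalance at its 95% limit (1.96 SE), the test statistic is shifted by 1.96*r* and has SD √(1 − *r*²). The two-sided rejection rate under no effect is then 5.3% at *r* = 0.1 and 7.9% at *r* = 0.3.

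**Step 4: precision gained by adjusting.** Residual variance falls by *r*², which is worth 60 × (1/(1 − *r*²) − 1) extra participants.

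| *r* | variance removed | SE ratio √(1 − *r*²) | gross gain of 60 | less about 1 for the degree of freedom |
|---|---|---|---|---|
| 0.1 | 1% | 0.995 | 0.6 | nil |
| 0.2 | 4% | 0.980 | 2.5 | 1.5 |
| 0.3 | 9% | 0.954 | 5.9 | 4.9 |

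At 25 per arm, the difference detectable with 80% power moves from 0.792 SD to 0.788, 0.776 or 0.756 SD.

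**Step 5: what these gains are measured against.** Step 4 compares adjustment for days with no covariate at all. The increment over a model that already holds the baseline value depends on a partial correlation that the article does not give. Any overlap between onset time and baseline severity in predicting outcome would reduce it.

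**The case against.** The strongest reply is that nothing here is an error. Restricting entry is a recognized way to control a prognostic factor, the article says why it did so, and citing a factor does not oblige a pilot to model it as well. Randomization makes the unadjusted comparison unbiased, and its standard error already contains the variation due to onset time. All of that stands. A reader might infer that the arm comparisons are biased or that the article contradicts itself; the documents support neither.

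A reader might also take the recovery figures as proof of a gradient within the first week. They are not. The article says that "patients who received medical attention within 7 days of onset had an approximately 56% recovery rate", against 27% for those presenting after 30 days. That contrast says nothing about day 1 against day 6, and narrowing a range usually weakens a correlation. The benefit may therefore be nil.

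Two further objections stand in part. Statistical Analysis names one conditional covariate but does not say that no other may be used, so it should not be read as forbidding onset time. And the outcomes concerned are labeled exploratory, in a trial without a power calculation.

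What survives is narrower. The comparison the article does specify leaves out a variable that it cites as prognostic and whose date must already be known to confirm eligibility, and including it costs little.

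**Conclusion.** The point holds as a minor analysis choice that can be improved. Onset time enters the trial only as an entry limit, and the stated arm comparisons neither balance on it nor adjust for it. The consequence is lost precision and exposure to chance imbalance, not bias and not an inflated overall type I error.

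The size is unknown. It ranges from nothing at an assumed *r* of 0.1 to roughly 2.5 to 6 participants' worth of 60 at 0.2 to 0.3, before the degree of freedom and any overlap with the baseline value are counted. Both the correlation and the uniform spread of days are my assumptions. Priority is low. The reason to act is that the change is nearly free and the pilot's effect estimates are meant to size later trials.

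**What to change.** In Statistical Analysis, make analysis of covariance the prespecified arm comparison for PTA and THI at each post-baseline visit (t1 to t5). The covariates would be the baseline value of the outcome, center, and days from onset to first trial treatment as a continuous variable. All three stay in the model whatever a baseline test shows. Making onset days mandatory while leaving baseline severity conditional would be hard to justify, so the two should change together. Name a rank-based or robust version of the same model for clearly nonnormal residuals, since the Mann-Whitney test takes no covariate.

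The cost is three degrees of freedom per model (two centers, two continuous covariates) and the replacement of the *t* test and Mann-Whitney test as the main comparison. No new data should be needed beyond the onset date, already required for eligibility, and the treatment start date. The Results section places analysis after publication of the protocol, and the statisticians are to stay blinded until it is complete, so the model can still be fixed before any comparison by arm.
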